| Single-lead telemetry     |                   | X  | X                | X | X | X | X | X | X | X |        |        |        |        |        |           |    | Day 5 through 8 are SC only. Telemetry is continuous from 12 h predose to 72 h postdose (IV cohorts) or 168 h postdose (SC cohorts). |
| Seated PR                 | X                 | X  | X                | X | X | X | X | X | X | X | X      | X      | X      | X      | X      | X         | X  | Day 1: Within 1 h before dosing and 5 to 15 min, 1 h (+ 30 min), and 8 h after starting dosing; Days 5-7 for SC cohorts only         |
| Body temperature          | X                 | X  | P                | X | X | X |   |   |   | X | X      | X      | X      |        |        | X         | X  | Any time before breakfast                                                                                                            |
| Seated BP                 | X                 | X  | X                |   |   |   |   |   |   |   |        | X      |        | X      |        | X         | X  | Day 1: 5 to 15 min and 1 h (+ 30 min) after starting dosing                                                                          |
| AOBPM                     |                   |    | P, 6 h           | X | X | X | X | X | X | X | X      |        | X      |        | X      |           |    | Days 5 through 7 are SC only. See Section 9.4.2. for more details.                                                                   |
| Adverse event reporting   | X                 | X  | ←-----→          |   |   |   |   |   |   |   |        |        |        |        |        | X         |    |                                                                                                                                      |

| Procedure               | Screening         |    | Treatment Period |   |   |   |   |   |   |        |        |        |        |        |        | Follow-up | ET | Notes |
|-------------------------|-------------------|----|------------------|---|---|---|---|---|---|--------|--------|--------|--------|--------|--------|-----------|----|-------|
|                         |                   |    | Week 1           |   |   |   |   |   |   | Week 2 | Week 3 | Week 4 | Week 5 | Week 7 | Week 9 | Week 13   |    |       |
| Day                     | Day -28 to Day -2 | -1 | 1                | 2 | 3 | 4 | 5 | 6 | 7 | 8      | 15 ±2  | 22 ±2  | 29 ±2  | 43 ±5  | 57 ±5  | 85 ±5     |    |       |

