#### 3.3. Benefit/Risk Assessment

LY3475766 has not been administered to humans. The nonclinical safety information for LY3475766 supports the transition from preclinical status to clinical development. Based on the mechanism of action and nonclinical data, LY3475766 is not considered to be a high uncertainty compound. The only potential risk that is anticipated relates to the finding of a nondose-dependent decrease in heart rate in a 1-month Good Laboratory Practice toxicology study that was performed in cynomolgus monkeys; there were no adverse events (AEs) or any significant electrocardiogram (ECG) findings associated with the decrease in heart rate. Refer to the IB for LY3475766 for more details. This risk is considered to be monitorable and manageable at the planned doses of 10 mg, 30 mg, and 1000 mg IV and 100 mg, 300 mg, and 600 mg SC for LY3475766 in dyslipidemic but otherwise healthy subjects.

More information about the known and expected benefits, risks, serious adverse events (SAEs), and reasonably anticipated AEs of LY3475766 can be found in the IB.

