**Figure GZEA.1. Dose escalation for Protocol J1T-MC-GZEA.**

Potential subjects will be screened to assess their eligibility to enter the study within 28 days prior to Day 1. In case of safety concerns, participants may be required to stay at the clinical site for a longer period at the discretion of the investigator. Subjects in all cohorts will return to the clinical research unit (CRU) as outpatients at predetermined visits for up to approximately 84 days postdose for follow-up assessments. In case a subject cannot come to the site for 1 or several outpatient visits, home visits may potentially be performed instead, depending on the circumstances and if agreed upon between investigator and sponsor.

Subjects will be confined at the CRU:

- from Day -1 (the day before dosing) to Day 4 (72 hours postdose) for IV cohorts (with outpatient visits starting on Day 8), and
- from Day -1 (the day before dosing) to Day 8 (168 hours postdose) for SC cohorts.

This is a randomized double-blinded SAD study in dyslipidemic but otherwise healthy male and female subjects investigating the safety, tolerability, PD, and PK of LY3475766 versus placebo.

Subjects will be enrolled in 6 cohorts:

- Cohort 1: 10 mg LY3475766 or placebo IV
- Cohort 2: 30 mg LY3475766 or placebo IV
- Cohort 3: 100 mg LY3475766 or placebo SC
- Cohort 4: 300 mg LY3475766 or placebo SC
- Cohort 5: 600 mg LY3475766 or placebo SC
- Cohort 6: 1000 mg LY3475766 or placebo IV

Safety and tolerability will be assessed throughout the study by means of vital sign measurements, safety laboratory tests, ECGs, physical examinations, automated office blood pressure monitoring (AOBPM), and AE recording. Sampling schedules, doses, and number of cohorts may be adjusted based on ongoing review of the PK, safety, and tolerability data. Additional follow-up visits may occur depending upon the PK and/or safety data.

Doses and the number of cohorts may be adjusted based on ongoing review of the PK, safety, and tolerability data at visits described in Section 2.

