#### **10.3.1.2. Statistical Evaluation of Safety**

Safety parameters that will be assessed include safety laboratory parameters, vital signs, and ECG parameters. The parameters will be listed and summarized using standard descriptive statistics.

The relationship between systolic BP, diastolic BP, and heart rate from AOBPM and the PK concentration will be evaluated through a longitudinal linear model with independent variables of PK concentration as a continuous variable and time relative to the first dose time as a categorical variable. A compound-symmetry variance-covariance structure will be used to model the within-subject correlation.

The mean systolic BP, diastolic BP, and heart rate by dose will be plotted against time. The maximum value (for each subject) within the 9 weeks after the first dose will be summarized and compared between dose groups using a linear model with dose as a factor and baseline mean value of the corresponding analysis variable as a covariate.

Additional analysis will be performed if warranted upon review of the data.

Baseline for safety parameters will be defined as the last evaluable value before the first dose.

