### **9.5.4 Vital signs**

Automated office blood pressure monitoring data (AOBPM) (systolic blood pressure, diastolic blood pressure and pulse rate) will be recorded. Four records are recorded, the first is discarded and for the latter 3 records, the mean will be calculated and used for reporting and analysing.

Vital signs data and AOBPM data will be summarized by treatment and timepoint together with changes from baseline, where baseline is defined as the Day 1 predose assessment. Figures of

mean vital signs and mean changes from baseline profiles over time will be presented by treatment.

Values for individual subjects will be listed.

The relationship between time-matched systolic blood pressure, diastolic blood pressure, and heart rate from AOBPM data and the LY3475766 PK concentration will be evaluated graphically using a scatter plot. The plot will include a longitudinal linear model with independent variables, PK concentration as a continuous variable and time relative to the first dose time as a categorical variable. A compound-symmetry variance-covariance structure will be used to model the within-subject correlation. If the model fails to converge, an alternative structure will be investigated instead. The estimated regression line and associated 90% CI will be fitted on the plot and the p-value for the slope reported.

Example of SAS code as follows.

```
proc mixed data=xxx;  
class time subject;  
model vital = pk_conc time /residual ddfm=kr;  
repeated time / subject=subject type=cs alpha=0.1;  
run;
```

For the AOPBM data, a repeated-measures statistical analysis of absolute and change from baseline vital sign measurements will be produced with fixed effects for treatment, timepoint, and the interaction treatment and timepoint and baseline as a covariate (for the change from baseline analysis). An unstructured covariance structure will be used and a compound symmetric structure can be used if the model fails to converge. The primary contrasts of interest are each dose level versus placebo at each timepoint. Least squares means as well as a 90% CI of the mean difference between each dose level and placebo will be obtained.

Example of SAS code as follows.

```
proc mixed data=xxx;  
class treatment;  
model change = baseline treatment timepoint treatment*timepoint  
/residual ddfm=kr;  
repeated timepoint / subject=subject type=UN;  
lsmeans treatment*timepoint / cl pdiff alpha=0.1;  
ods output lsmeans=lsm diffs=estims;  
run;
```

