For the AOPBM data, for each subject, the maximum value within the 3 and 9 weeks after the first dose will be summarized by treatment, and listed.

In addition, the calculated maximums values will be compared between dose groups using a linear model with treatment as a fixed effect and baseline value as a covariate. The analysis will compare each dose of LY3475766 against placebo. Least-squares means as well as 90% CIs for the difference of LY3475766 compared with placebo will be reported.

Example of SAS code as follows.

```
proc mixed data=xxx;  
class treatment;  
model max = baseline treatment /residual ddfm=kr;  
lsmeans treatment / cl pdiff alpha=0.1;  
ods output lsmeans=lsm diffs=estims;  
run;
```

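### Pulse rate gets a per-subject maximum but no minimum, although the only anticipated risk is a fall in heart rate, and the maximum is taken over more readings in SC than in IV cohorts

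*Combined protocol and SAP*

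**What the plan says.** SAP 9.5.4 defines the AOBPM data as systolic pressure, diastolic pressure and pulse, each the mean of the last three of four records. For these data, per subject, "the maximum value within the 3 and 9 weeks after the first dose will be summarized by treatment, and listed". A linear model with treatment and baseline then compares each dose with placebo (least-squares means, 90% CIs). Protocol 10.3.1.2, just after naming heart rate among the variables, plans the same statistic for one window: "The maximum value (for each subject) within the 9 weeks after the first dose will be summarized and compared between dose groups". Neither document plans a per-subject minimum or a count of low pulse values.

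Protocol 3.3 gives the direction of the safety question: "The only potential risk that is anticipated relates to the finding of a nondose-dependent decrease in heart rate", seen in a monkey toxicology study.

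The Schedule of Activities has AOBPM predose and at 6 h on Day 1, then on Days 2 to 8, 15, 29 and 57, with the note "Days 5 through 7 are SC only". This follows from confinement, which ends on Day 4 for IV and Day 8 for SC cohorts. SAP section 6 pools placebo over cohorts, hence over routes.

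SAP 9.5.4 also plans by-timepoint summaries, a repeated-measures model of each dose against placebo at each timepoint, and a model of pulse on drug concentration.

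**The concern.** A per-subject extreme is meant to show whether individuals reached worrying values. For blood pressure the maximum is a reasonable choice. For pulse rate the stated risk lies at the other end. If the drug lowers pulse for only part of the window, the subject's maximum tends to come from readings outside the affected period, so the comparison understates the fall.

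A second issue affects any extreme, high or low, and blood pressure as well as pulse. The expected maximum grows with the number of readings, and SC subjects have three more than IV subjects. Against placebo pooled over routes, SC doses then look slightly high and IV doses slightly low with no drug effect. The model for the maximum has no route term to absorb this.

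At stake is the interpretability of one planned table on the one risk the protocol anticipated.

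**Working it through.** **No stated figure to reproduce.** The documents give no pulse-rate SD, effect size or power, and SAP section 7 says the study is not powered on hypothesis testing. The bpm results below rest on assumptions. The reading counts do not.

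**Step 1. Scheduled postdose AOBPM readings.**
- IV, 3 weeks: Day 1 at 6 h, Days 2, 3, 4, 8, 15 = 6.
- SC, 3 weeks: the same plus Days 5, 6, 7 = 9.
- Adding Days 29 and 57 for 9 weeks: IV 8, SC 11.

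**Step 2. Route bias with no drug effect.** For n independent normal readings, the expected maximum in within-subject SD units is E(n) = ∫ x·n·φ(x)·Φ(x)^(n-1) dx. This gives E(6) = 1.267, E(8) = 1.424, E(9) = 1.485 and E(11) = 1.586.
- 3 weeks: 1.485 - 1.267 = 0.218 SD between SC and IV.
- 9 weeks: 1.586 - 1.424 = 0.163 SD (from unrounded values).

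Planned placebo is 12 subjects over six cohorts, three per route, so I assume half IV and half SC. Each route is then off by half the gap: 0.109 SD and 0.081 SD. With a within-subject SD of 5 bpm these are 0.54 and 0.41 bpm, up for SC and down for IV; simulation gave about 0.4 at 9 weeks and 0.5 to 0.6 at 3 weeks. Over SDs of 3 to 8 bpm the range is 0.3 to 0.9 bpm (3 weeks) and 0.2 to 0.7 bpm (9 weeks). With a serial correlation of 0.6 per day the SC-IV gaps shrink to 0.156 and 0.109 SD.

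**Step 3. Sensitivity to a fall, 9-week window.** Simulated trials of 48 subjects (6 active and 2 placebo per cohort), the SAP's baseline-adjusted model and pooled placebo. Assumed: between-subject SD 8 bpm, within-subject SD 5 bpm, independent readings, and an 8 bpm fall at every dose until the day shown. The percentage is the share of 90% CIs per dose lying below zero.

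| Fall lasts to | Maximum, as planned | Minimum, common timepoints |
|---|---|---|
| Day 8 | about -3 bpm, 26-30% | -6.7 bpm, 78-80% |
| Day 15 | about -4 bpm, 39-44% | -7.2 bpm, 83-85% |
| whole window | -7.5 to -8.3 bpm, 87-93% | similar |

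For a fall to Day 29 the planned maximum shows about -5.6 bpm and 61-66%. Over all scheduled readings rather than common ones, the minimum for a fall to Day 15 shows -6.8 to -8.1 bpm and 81-92%. The upper end is inflated in SC doses by the same unequal counts, so the common-timepoint figures are the fair comparison.

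The pattern holds under other assumptions. With a 10 bpm fall and within-subject SD 4 to 6 bpm, a fall on Days 8 to 29 only moves the 9-week maximum by -0.7 to -1.5 bpm and the minimum by -5.9 to -7.7 bpm. A fall from dosing to Day 15 fills every reading in the 3-week window, so the 3-week maximum moves by the full amount.

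**Step 4. Minimum or largest decrease?** For subject i, the change at the lowest reading is min(Y_i) - B_i, where B_i is baseline. With B_i as covariate, subtracting it from the response lowers the baseline slope by exactly 1 and leaves the treatment contrasts unchanged. The two analyses give identical differences from placebo.

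**The case against.** The strongest reply is that a fall would be seen elsewhere. The repeated-measures model gives each dose against placebo at each visit, and the SAP calls these the primary contrasts of interest. Under the Step 3 assumptions, a by-visit baseline-adjusted comparison approximating that model estimates the full -8 bpm at an affected visit, and its CI excludes zero in 74-78% of runs. SAP 9.1 puts minimum and maximum in the standard summaries, so the lowest pulse per dose at each visit is reported and individual values are listed. The concentration model adds a further look. All of this stands. A reader might infer that a fall in pulse could go unseen; the documents do not support that.

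A reader might also infer that the maximum is blind to a fall. It keeps roughly a third to a half of the simulated falls ending by Day 8 or 15, and all of one lasting the window. The documents give no time course, so neither case can be presumed.

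The route bias is also small: about 0.4 bpm at 9 weeks against a 90% CI half-width of 4.4 bpm, with 11-12% of null CIs excluding zero against a nominal 10%. Finally, neither the escalation and interruption rules in protocol 7.4.1 nor the primary endpoints use this maximum.

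What survives is narrower. The visit-wise and concentration models address means, and a by-visit minimum is one value per group per visit. None compares subjects' lowest pulse over the window with placebo. ECG heart rate does not fill the gap, because SAP 9.5.5 says ECGs will not be presented.

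**Conclusion.** The point holds as a limited gap. For pulse rate, the only per-subject extreme compared with placebo is the one facing away from the anticipated risk. Under SDs of 8 and 5 bpm and an 8 bpm fall to Day 15, the 9-week maximum recovers about half the effect and roughly 40% of CIs fall below zero, against about -7 bpm and 84% for the minimum on common timepoints. The advantage disappears if the fall lasts the whole window. These sizes depend on the assumed SDs, independent readings and the assumed duration of effect.

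The unequal reading counts are a fact of the schedule, but their effect is small: about ±0.4 bpm at 9 weeks and up to ±0.6 bpm at 3 weeks with a within-subject SD of 5 bpm. A minimum would carry the same bias in the opposite direction, so both parts should be corrected together.

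Severity is minor to moderate. A reader might take this as a flaw that undermines the safety assessment; with the visit-wise model, by-timepoint summaries and concentration model in place, it does not.

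**What to change.** In SAP 9.5.4:

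- For AOBPM pulse rate, add each subject's minimum within 3 and 9 weeks and analyse it in the same model against placebo. A separate largest-decrease analysis is unnecessary with baseline as covariate.
- Tabulate by treatment the number of subjects with any postdose AOBPM pulse at or below 50 bpm. This is a descriptive cut taken from the protocol's own entry threshold (exclusion criterion 24).
- Keep the maximum, which the protocol specifies and which suits blood pressure.
- Compute all extremes, for pulse and blood pressure, over the timepoints scheduled for both routes, omitting Days 5 to 7. Counts become 6 and 6 at 3 weeks, 8 and 8 at 9 weeks, which removes the route imbalance.

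The cost is one derived variable and one further table, with no new data or visits. The downside is that SC readings on Days 5 to 7 leave the extreme comparison, so an SC effect confined to those days would not appear there. Those readings are still listed, summarised by visit and included in the repeated-measures model.

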### 9.5.5 Electrocardiogram (ECG)

ECGs will be performed for safety monitoring purposes only and will not be presented. Any clinically significant findings from ECGs will be reported as an AE.

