**Table GZEA.1. Objectives and Endpoints**

| Objectives                                                                                                                                                                                                                                                                                               | Endpoints                                                                                                                                                                                           |
|----------------------------------------------------------------------------------------------------------------------------------------------------------------------------------------------------------------------------------------------------------------------------------------------------------|-----------------------------------------------------------------------------------------------------------------------------------------------------------------------------------------------------|
| Primary 
 
To assess the safety and tolerability of single IV and SC doses of LY3475766 in dyslipidemic but otherwise healthy subjects.
 
                                                                                                     | 
 
Incidence of AEs and SAEs
 
Clinically significant changes in vital signs, safety laboratory parameters, and ECGs
 
                          |
| Secondary 
 
To characterize the PK of LY3475766 following single doses in dyslipidemic but otherwise healthy subjects.
 
To characterize the PD of LY3475766 following single doses in dyslipidemic but otherwise healthy subjects.
 
 | 
 
AUC, <math>C_{\max}</math>, and <math>t_{\max}</math>
 
Absolute and percent change from baseline in fasting levels of TG, LDL-C, and apoB
 
 |

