#### **9.4.4. Electrocardiograms**

For each subject, a single 12-lead digital ECG will be collected according to the Schedule of Activities (Section 2). Electrocardiograms must be recorded before collecting any blood samples. Subjects must be supine for approximately 5 to 10 minutes before ECG collection and remain supine but awake during ECG collection. Electrocardiograms may be obtained at additional times, when deemed clinically necessary. All ECGs recorded should be stored at the investigational site.

Electrocardiograms will be interpreted by a qualified physician at the site as soon after the time of ECG collection as possible, and ideally while the subject is still present, to determine whether the subject meets entry criteria at the relevant visit(s) and for immediate subject management, should any clinically relevant findings be identified. The screening ECG may be initially reviewed by a qualified non-physician designated by the investigator but must be reviewed by a physician to confirm eligibility before randomization.

Any clinically significant findings from ECGs that result in a diagnosis and that occur after the subject receives the first dose of the investigational product should be reported to Lilly, or its designee, as an AE via eCRF.

If a clinically significant finding is identified (including, but not limited to, changes in QT/QT interval corrected for heart rate [QTc] interval from baseline) after enrollment, the investigator will determine if the subject can continue in the study. The investigator, or qualified designee, is responsible for determining if any change in subject management is needed, and must document his/her review of the ECG printed at the time of collection.

Collection of ECG replicates at a particular time point will be permitted to ensure high-quality records.

Starting at Day 1, all digital ECGs (scheduled and unscheduled) will be electronically transmitted to a central ECG laboratory designated by Lilly. The central ECG laboratory will perform a basic quality control check (for example, demographics and study details) and then store the ECGs in a database. At a future time, the stored ECG data may be overread at the central ECG laboratory for further evaluation of machine-read measurements or to meet regulatory requirements.

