## **11. CHANGES FROM THE PROTOCOL SPECIFIED STATISTICAL ANALYSES**

There were no changes from the protocol specified statistical analyses.

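### SAP 9.5.5 withdraws the ECG listings and summaries that protocol 10.3.1.2 promises, and SAP 11 declares that nothing changed

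*Combined protocol and SAP*

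**What the plan says.** The primary endpoint in protocol Table GZEA.1, repeated in the synopsis, includes "Clinically significant changes in vital signs, safety laboratory parameters, and ECGs".

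Protocol 10.3.1.2 sets out the reporting in two consecutive sentences. The first names what is covered: "Safety parameters that will be assessed include safety laboratory parameters, vital signs, and ECG parameters". The second says how: "The parameters will be listed and summarized using standard descriptive statistics". No condition is attached.

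SAP 9.5.5 has two sentences on ECGs. The first reads "ECGs will be performed for safety monitoring purposes only and will not be presented". The second leaves one route open: "Any clinically significant findings from ECGs will be reported as an AE".

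SAP 3 gives the SAP precedence over the protocol's statistical section, but undertakes to identify considerations that differ substantially. SAP 11 is the place for that, and it says "There were no changes from the protocol specified statistical analyses".

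**The concern.** The two documents give opposite instructions on the same data, and the section meant to record departures says there are none. A reader who relies on SAP 11 would expect ECG tables in the study report and find none.

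The setting gives this weight. This is a first-in-human study, and protocol 3.3 says of its risk profile: "The only potential risk that is anticipated relates to the finding of a nondose-dependent decrease in heart rate". Several eligibility criteria also concern slow heart rate and conduction, including a prolonged PR interval. Without interval data by dose, the report can say that no clinically significant ECG finding was recorded, or which ones were. It cannot show whether PR, QRS or QTc moved with dose.

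**Working it through.** The plan states no power, alpha or effect-size figure for ECGs, so this is a comparison of texts followed by a count.

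**1. Is there a reading that reconciles the texts?**
- Protocol 10.3.1.2 refers to ECG parameters, meaning measured values, not only to events. AE reporting alone does not meet it.
- SAP precedence (SAP 3) could settle which instruction applies, but only together with the promised declaration. SAP 11 does not make one.
- SAP 9.1 promises listings of all data held in the database, and SAP 9.5.9 lists even safety assessments that section 9.5 does not detail. SAP 9.5.5 therefore also sits badly with the SAP's own general rules.
- Protocol 9.4.4 foresees machine-read intervals and heart rate being used for analysis and reporting, replaced by overread values if an overread is done before the final report. The protocol did not treat ECGs as bedside monitoring only.

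No reconciling text was found.

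**2. How are the three components of the endpoint treated in the SAP?**

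| Component | SAP section | Output |
|---|---|---|
| Laboratory | 9.5.3 | Chemistry and hematology summarized by treatment with change from baseline; listed |
| Vital signs | 9.5.4 | Summarized by treatment and timepoint with change from baseline; plotted; listed; AOBPM also modelled |
| ECG | 9.5.5 | Clinically significant findings as AEs only |

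**3. What is lost and what remains?**

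| Quantity | Output that remains |
|---|---|
| Clinically significant ECG finding in a subject | AE listings and tables |
| Group-level heart rate | Pulse-rate summaries from vital signs and AOBPM; AOBPM repeated-measures model, each dose versus placebo at each timepoint with 90% CI; AOBPM heart rate against concentration |
| ECG-derived (supine) heart rate | None |
| PR, QRS, QT, QTcF | None |

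**4. How many records are affected?**

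Inputs: the 12-lead ECG row of the Schedule of Activities (Day 1 predose, 6 h and 12 h; Days 2, 8, 29 and 85) and the evaluable target of 48 (36 active, 12 placebo).

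- Post-dose ECGs per completing subject: 2 on Day 1 + 4 later = 6.
- Evaluable target: 6 × 48 = 288, of which 6 × 36 = 216 active and 6 × 12 = 72 placebo.
- With the predose record: 7 × 48 = 336.
- Upper bound if all 70 permitted subjects were enrolled and completed: 6 × 70 = 420.

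These are counts of records not displayed. They do not measure any ECG effect.

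**The case against.** The strongest reply is that the endpoint is worded as clinically significant changes, and SAP 9.5.5 sends exactly those to the AE tables. This stands. A reader might infer that a component of the primary endpoint goes unreported, and the documents do not support that. Nor is the AE route strictly confined to diagnoses. Protocol 9.4.4 requires an AE for "Any clinically significant findings from ECGs that result in a diagnosis", but SAP 9.5.5 carries no such condition, and the AE definition in protocol Appendix 1 covers any unfavorable sign. Under either wording, though, the route carries only findings judged significant in an individual subject. It cannot show a shift in group means.

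The second reply is that the one anticipated risk is well covered elsewhere. This also largely stands. It is tempting to conclude that a fall in heart rate would never appear. But seated pulse rate is scheduled at every visit, AOBPM on most early days and on Days 15, 29 and 57, and SAP 9.5.4 compares each dose with placebo over time. Two small gaps remain. Neither AOBPM nor seated pulse is scheduled at 12 h on Day 1, when an ECG is. The AOBPM extreme-value summary takes each subject's maximum, which is a poor tool for a decrease, but it only supplements the model. Pulse rate carries no information on conduction or repolarization.

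Third, the study is descriptive and not powered, and protocol 3.3 reports no significant ECG findings with the heart-rate decrease in monkeys. Both are true. They limit the consequence but do not remove the protocol's commitment to descriptive ECG summaries.

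**Conclusion.** The protocol-SAP conflict is real and undeclared. SAP 9.5.5 removes output that protocol 10.3.1.2 promises, and the statement in SAP 11 is wrong as it stands.

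The consequence is specific: no display by dose of PR, QRS, QT/QTcF or ECG-derived heart rate, and about 288 scheduled post-dose ECGs untabulated. The report could not show a sub-clinical group shift in conduction or repolarization, nor show its absence. The point does not extend to clinically significant findings or to a group fall in heart rate, both of which have reporting routes. No planned estimate or test is affected.

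The count assumes that 48 subjects complete every scheduled ECG. The Safety population is everyone dosed, so the actual number could be higher with replacements or lower with missed visits.

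**What to change.** Replace SAP 9.5.5 so that ECG heart rate, PR, QRS, QT and QTcF are listed, and summarized descriptively by treatment and timepoint, with change from Day 1 predose. That is the last scheduled ECG before dosing, so it fits the protocol's baseline definition. Use the machine-read values, or the overread values if an overread is done, as protocol 9.4.4 foresees. Keep the sentence sending clinically significant findings to AEs, and align its wording with protocol 9.4.4 on whether a diagnosis is required.

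Correct SAP 11 so that it identifies any departure that remains. Declaring and justifying the omission there would cure the false statement, but would still leave the interval data unshown.

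Counts of subjects crossing the eligibility limits (seated heart rate of 50 or below, PR of 220 msec or above) are not needed. Those limits govern entry, study ECGs are supine, and the protocol promises only listings and standard descriptive statistics.

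The cost is a SAP revision, a few standard tables and a transfer of stored data. Digital ECGs from Day 1 onward already go to the central ECG laboratory, so no new measurements are required. QTcF is already in the SAP's abbreviation list, but its derivation would need to be specified.
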